## Interventions

The intervention this study will investigate is the use of the MAINTAIN instrument to guide the classification of patients and stratification of the MC approach. Specifically, the MAINTAIN instrument score will be used in combination with patients’ response to initial chiropractic care to determine their stratification within a tailored MC approach. This stratified strategy (Stratified MC) is based on prior investigations observing that both clinical response and psychosocial profiles contribute to MC outcomes [17, 44, 45].

### Initial care

As shown in Fig. 1, this trial will comprise two arms, of which all participating patients will receive pragmatic chiropractic care for the initial 3 weeks (6 visits) with interventions tailored to each patient based on clinicians’ judgment. After the initial treatment period, each patient will initiate the allocated intervention: Stratified MC (intervention arm) or Standard Chiropractic Care (control arm).

#### Stratified MC—intervention arm

The Stratified MC group will be first classified by their response to the initial 6 visits using the global perceived change score (GPC) collected at their 3-week (Questionnaire 1): *responding* (GPC score = 5) or *not responding* to care (GPC score ≤ 4). Based on their GPC score, participating patients will be further stratified based on their MAINTAIN score. A MAINTAIN score ≤ 21 is classified as *not a candidate for MC*, and a MAINTAIN score of ≥ 22 is classified as a *very good candidate for MC*. A combination of both the GPC and MAINTAIN scores will determine the stratification to one of the following groups:*Stratified Chiropractic Care (SCC):* Participating patients classified as *not responding* (GPC score ≤ 4) to the initial 3 weeks of care will be offered an alternative treatment based on clinicians’ judgment, which will be recorded. Home exercises will be recommended.*Symptom Guided Care (SGC):* Participating patients classified as *responding* (GPC score = 5) to the initial 3 weeks of care and *not a candidate for MC* (MAINTAIN score ≤ 21) will return for further interventions and manual treatment if they have a relapse or exacerbation of symptoms. Home exercises will be recommended.*Maintenance Care (MC):* Participating patients classified as *responding* (GPC score = 5) to the initial 3 weeks of care and *very good candidate for MC* (MAINTAIN score ≥ 22) will be recommended MC with pre-planned visits at 4–12-week intervals (aiming at increasing the interval as soon as possible), including tapering manual treatments and home exercise recommendations. Participants in this group can return to the clinic in between their pre-scheduled visits in case they experience a flare-up. The rationale behind choosing only the higher category for MC (MAINTAIN score ≥ 22) in this trial is related to the instrument’s sensitivity and specificity. Within the middle category, “MAINTAIN score 18–21,” the uncertainty is higher for misclassification of the psychological profile (AC vs. DYS), and a more shared decision-making process is required in clinical practice to determine the most suitable treatment strategy. This does not align well with the design of this randomized trial, where one group must follow the assigned intervention. Therefore, the higher cutoff was used to ensure that the correct patients receive the most appropriate treatment strategy in the intervention group, thereby minimizing the risk of AC receiving MC.

#### Standard chiropractic care (SCC)—control arm

Participating patients will receive a SCC in which treatment will be provided based on clinicians’ judgment and home exercise recommendations. This may or may not include MC depending on clinicians’ standard operating procedures. All treatments provided will be recorded.

#### All groups

Initial care will include home exercise recommendations with progression tailored to each participant based on their initial assessment. In addition, participants will be encouraged to increase physical activity based on their preferences and functional limitations (i.e., walking program, bike, swimming). Participants will be instructed to increase activity using graded activity principles [53]. All patients will be given an infographic with graded activity guidelines (e.g., pacing, quotas). In addition, all groups will receive interventions based on clinicians’ judgment and reassuring messages focusing on developing self-efficacy while encouraging the minimization of kinesiophobia, catastrophizing, and passive coping behaviors, in accordance with contemporary pain science.

Once completed participation, a purposeful sample of chiropractors and patients from both groups will be invited for semi-structured qualitative interviews to explore their experience of being part of the study to get a further understanding of barriers and facilitators for using the MAINTAIN instrument. A semi-structured interview guide will be developed a priori. One-to-one interviews will be conducted by one of the investigators using a virtual platform (Zoom Video Communications, Inc., CA, USA). The session will be recorded, transcribed verbatim. We will aim to recruit a convenient sample of 12–15 participants per group (chiropractors and patients) that completed the study intervention to be interviewed.

### Concomitant care

Given that this is a pragmatic study, the concomitant use of other treatments and interventions will not be restricted during the study. The intervention will not interfere with other regular medical care and medications, which will continue as usual during the study.

### Outcome measures

Our primary outcome measure is the number of days with activity-limiting pain (recorded via SMS) measured bi-weekly over 12 months. Secondary outcome measures include missed working days due to pain, loss of work productivity due to pain, pain intensity, global perceived change, self-reported activity limitation, self-rated health, and pain self-efficacy. Table 2 shows all outcome measures recorded in the SMS and electronic questionnaires.

**Table 2 Tab2:** Summary of outcome measures

Time point	Questionnaire	Patient outcome measures	Clinician outcome measure
Every 2 weeks	SMS	- Total number of days with activity limiting pain in the past 2 weeks - Total number of missed workdays due to pain in the past 2 weeks - Experienced loss of productivity at work due to pain in the past 2 weeks	
First visit (baseline)	0	- Demographic data - Inclusion criteria - Pain intensity (NRS) [54] - Disability (Neck Disability Index [55]/Roland-Morris Disability Questionnaire [56]) - MAINTAIN instrument [49] - Health-related QOL (EQ-5D-5L) [58] - Self-efficacy (Pain Self-Efficacy) [59] - Physical Activity (IPAQ) [60] - Expectations	- Clinical impression - Implementation data
3 weeks	1	- Global Perceived Change [61] - Adverse events - Pain intensity (NRS) - Disability (Neck Disability Index or Roland-Morris Disability Questionnaire) -MAINTAIN instrument - Health-related QOL (EQ-5D-5L) - Self-efficacy (Pain Self-Efficacy) - Physical Activity (IPAQ) - Expectations	- Implementation data - Clinical impression - Date of visits and content (since last follow-up)
3 months	2		
6 months	3		
12 months	4		

### Baseline and follow-up assessments

A summary of baseline and follow-up assessments is detailed in Table 2. Baseline data (Questionnaire 0) will be collected from both clinicians and patients at the first visit. Clinician data will include implementation data as well as their clinical impression of the patient. Patient data will be collected on demographics, current pain (numeric pain scale (NRS) [54]), pain in the past week (NRS), activity limitation/disability (neck disability index (NDI) [55]/Roland-Morris Disability Questionnaire (RMDQ) [56]), psychological and behavioral consequences of pain (MPI [57]), self-rated health (EQ-5D [58]), the MAINTAIN instrument [49], beliefs of patients on their ability to function with pain (pain self-efficacy questionnaire [59]), physical activity (International Physical Activity Questionnaire (IPAQ) [60]), and expectations of treatment.

Follow-up assessment (Questionnaire 1–4) will be completed at 3 weeks, 3 months, 6 months, and 12 months, also collecting data from clinicians and patients. Practitioners will provide data on implementation and clinical impression of the patient, as well as expectations of care if the patient is receiving MC (Yes/No), and the date and content of treatment visits. In addition to these questionnaires, patients will also receive an SMS every 2 weeks to collect data on activities limited due to pain in the last 0–14 days, missed working days due to pain, and loss of work productivity due to pain. Figure 2 presents the schedule of participating practitioners’ and patients’ enrollment, interventions, and assessments.

**Fig. 2 Fig2:**
[figure not shown]
Schedule of participant enrollment, interventions, and assessments

### Safety monitoring

A Data and Safety Monitoring Board (DSMB) will monitor participant safety, data quality, and the progress of the trial. The DSMB includes a physiotherapist with expertise in patient safety and two chiropractors: one with expertise in clinical trials and one with expertise in patient safety. The DSMB will communicate frequently via email throughout the study, formally meet every 6 months, and monitor data quality and adverse events. While there is no pre-planned auditing of the trial, the institutional research ethics board may perform post-approval monitoring and auditing of the trial conduct.

Based on the literature, for both groups, we anticipate only mild adverse events (AEs) commonly reported following chiropractic treatments, such as mild discomfort/pain and stiffness [62, 63]. All patient follow-up questionnaires will include specific questions about AEs. If an AE is reported, the principal investigators will be notified immediately via email for documentation and reporting in the final manuscript. Upon notification, at least one of the principal investigators will review the AE report by accessing the participant’s response on REDCap and identify the type of AE and severity based on pre-defined criteria [64]. If any serious adverse event (SAE) that interferes with study protocol compliance is identified, it will be reported to the ethics board, the respective chiropractor will be notified, and patients will be instructed to discontinue the study.

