### Data collection

The automated SMS track, via Twilio System, will be used to collect SMS, and REDCap will be used to collect electronic questionnaire data. Each participating clinician will complete an initial questionnaire (Questionnaire 0-clinician) to record their individual characteristics.

Upon Questionnaire 0-patient completion, participating patients will be automatically registered in the Twilio system, given a confidential study ID linked to the clinician from which they are receiving treatment, and automatically scheduled to receive 3 questions via SMS every 2 weeks for 12 months. The follow-up questionnaires (Questionnaire 1–4) will be automatically sent via e-mail to both participating patients and clinicians at 3 weeks, 3, 6, and 12 months, respectively.

Data collection will be monitored daily in real-time, and contact with participating patients and clinicians will ensure high response rates. Specifically, in case of email delivery notification from REDCap or identification of incomplete questionnaires, email reminders will be sent to participating patients and clinicians.

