### Provisions for post-trial care

As no adverse events beyond normal transient mild discomfort/pain are expected, no follow-up plans will be included in this study.

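### Adverse events are asked about only three times in the 49 weeks when the strategies differ, with a gap of up to 26 weeks, so mild transient events are likely to be missed and notification can come late

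*Protocol article*

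**What the plan says.** The Safety monitoring section states that "All patient follow-up questionnaires will include specific questions about AEs". It then sets out what follows a report: an e-mail to the principal investigators, their review of the participant's REDCap response, grading of type and severity, and onward reporting of certain serious events. The questionnaires are "automatically sent via e-mail to both participating patients and clinicians at 3 weeks, 3, 6, and 12 months, respectively" (Data collection), and the section on baseline and follow-up assessments gives the same times: "Follow-up assessment (Questionnaire 1–4) will be completed at 3 weeks, 3 months, 6 months, and 12 months".

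Two other channels run alongside. Patients are "automatically scheduled to receive 3 questions via SMS every 2 weeks for 12 months" (Data collection). Table 2 identifies the three questions as activity-limiting days, missed workdays and lost productivity. Clinicians record implementation data, clinical impression, and the dates and content of visits. Table 2 lists AEs only in the patient column.

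On treatment timing, both arms first receive three weeks (six visits) of care at the clinician's judgment. The Initial care section continues: "After the initial treatment period, each patient will initiate the allocated intervention". On the kind of event expected, Safety monitoring anticipates mild discomfort or pain and stiffness, and the section on post-trial care says: "As no adverse events beyond normal transient mild discomfort/pain are expected, no follow-up plans will be included in this study".

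**The concern.** The strategies under comparison apply from week 3 to week 52, and in that period the scheduled AE questions are far apart. The longest gap, weeks 26 to 52, covers about half of it. Soreness or stiffness that lasts a few days is hard to report accurately months later. If the questionnaire item looks back over a shorter period, events before that period are never asked about.

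Two things are at stake. The first is the completeness of the harms data, which the Dissemination plans commit to report under the CONSORT-Harms extension and which Appendix 1 includes in its definition of Effectiveness. The second is timeliness: the alert to the principal investigators depends on a questionnaire answer, so it can follow onset by months while visits continue.

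**Working it through.** The article states no figure for the AE interval, so there is none to reproduce. The check works from the stated times.

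**Inputs.** AE questions at 3 weeks and 3, 6 and 12 months (Data collection; Baseline and follow-up assessments), taken as weeks 3, 13, 26 and 52. Common initial care in weeks 0–3 with six visits (Initial care). Maintenance care visits every 4–12 weeks (Stratified MC). SMS every 2 weeks (Data collection).

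**1. Gaps.** 3 − 0 = 3; 13 − 3 = 10; 26 − 13 = 13; 52 − 26 = 26 weeks.

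**2. Frequency of asking.** Weeks 0–3: one question in 3 weeks. Weeks 3–52: three questions in 49 weeks, or 49/3 = 16.3 weeks per question, which is 16.3/3 = 5.4 times sparser. The last gap is 26/49 = 53% of the period in which strategies differ.

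**3. Delay from onset to the next question.** With onset uniform in time, the mean delay is ΣL²/(2ΣL) over gaps L.
- Weeks 0–52: (9 + 100 + 169 + 676)/(2 × 52) = 954/104 = 9.2 weeks.
- Weeks 3–52: (100 + 169 + 676)/(2 × 49) = 945/98 = 9.6 weeks.
- Weeks 0–3: 1.5 weeks.
- Fortnightly item: mean 1 week, maximum 2.

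The maximum under the plan is 26 weeks if all questionnaires are returned on time. If the 6-month questionnaire is missed, the gap is 52 − 13 = 39 weeks.

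**4. Coverage under a fixed look-back (assumed, since none is stated).** Share of weeks 3–52 covered = Σ min(look-back, L)/49.

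| Look-back | Weeks 3–52 covered |
|---|---|
| 2 weeks | 6/49 = 12% |
| 4 weeks | 12/49 = 24% |
| 8 weeks | 24/49 = 49% |
| 13 weeks | 36/49 = 73% |

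**5. Illustration with fading recall (assumed).** Capture in a gap of length L is (1 − e^(−kL))/(kL), with k = ln 2/half-life. At a 4-week half-life, capture is 78%, 48%, 40% and 22% for the four gaps.

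For the maintenance care stratum, assume events proportional to visits and one visit per 8 weeks. Visits per gap are then 6, 1.25, 1.625 and 3.25, a total of 12.1. The true share of events in initial care is 6/12.1 = 49%, but its share of captured events is 71%. Over half-lives of 2–13 weeks the captured share runs from 78% to 59%. At the 4-week half-life, 4-weekly visits give 55% captured against 33% true, and 12-weekly visits give 78% against 60%. A fortnightly item would capture 72–95% over half-lives of 2–13 weeks.

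**6. The same schedule counted per visit.** Initial care has six visits per AE question. In the maintenance care stratum after week 3 there are 49/12/3 = 1.4 to 49/4/3 = 4.1 visits per question, and 26/12 = 2.2 to 26/4 = 6.5 in the last gap.

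**The case against.** A reader might infer that the schedule biases the harms comparison, or pulls it towards no difference because closely observed common care is pooled with loosely observed differing care. The documents do not support that. Both arms have the same schedule, so it does not in itself produce differential ascertainment. No pooled 52-week AE comparison is stated, and how AEs are tabulated belongs to the analysis plan, which is not shown. Answers arrive by questionnaire, so the week-3 data can already be separated from the rest.

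It is also tempting to say that capture is densest when the arms cannot differ. Asking is densest per week but not clearly per visit (step 6). And although no difference is intended in weeks 0–3, clinicians learn the allocation at the first visit and treat unblinded, so one is possible.

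A 26-week recall period should not be read into the text. The item wording is not given, and 26 weeks is only the interval between questions. Nor does an event necessarily go unnoticed for that long: patients may tell their chiropractor, the coordinator contacts clinicians monthly, and the SMS records activity-limiting pain. None of these is described as an AE route. The full protocol, not shown, may contain one.

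Finally, asking at every follow-up questionnaire is a defensible choice in a pragmatic trial of usual-type care where only mild events are expected, and a fourth SMS question would load the channel that carries the primary outcome.

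What stands is the schedule itself. The article traces the reporting chain from questionnaire answer to investigator review, so the criticism concerns what it fixes and not a detail left out in condensing.

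**Conclusion.** The point holds as one of under-capture and late detection, and the change is a worthwhile low-cost improvement rather than the correction of an error. Three scheduled AE questions in 49 weeks, a longest gap of 26 weeks and a mean delay of 9.6 weeks follow from the stated times, with uniform onset assumed for the mean and on-time return for the maximum. That mild, transient events will be under-captured is a judgment from the expected event type. Its extent cannot be derived from the documents: coverage of weeks 3–52 ranges from 12% to 73% over assumed look-backs of 2–13 weeks. The fading-recall percentages illustrate the maintenance care stratum only, under assumed recall and visit rates, and should not be quoted as expected results for the trial.

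**What to change.** - Add one yes/no AE item to the fortnightly SMS, placed after the three existing questions so that the primary outcome is answered first. A yes should open the REDCap AE form and trigger the existing e-mail to the principal investigators.
- Add an AE field to the clinician's existing record of visit dates and content. Keep this source identifiable: clinicians are unblinded and visit frequency may differ between arms, so the SMS item and questionnaires are the fairer basis for comparing arms.
- Flag patients enrolled before the change by ascertainment version, and stratify by that flag or restrict the AE summaries accordingly.
- Since AE answers are already dated by questionnaire, it is sensible to show weeks 0–3 and weeks 3–52 separately by arm.

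These changes affect measurement only. With recruitment planned to May 2026 and data collection to July 2027, an amendment made during that time would still reach patients in follow-up. The costs are a slight response burden on the primary-outcome channel, more AE reports for the principal investigators to review, AE counts that will rise because more is asked, and an ethics amendment.

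### Reporting of a serious adverse event to the ethics board and the chiropractor depends on interference with protocol compliance, not on seriousness

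*Protocol article*

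**What the plan says.** All the relevant text is in the Safety monitoring section of the protocol article, which sets two tiers.

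- **Any reported adverse event.** "If an AE is reported, the principal investigators will be notified immediately via email for documentation and reporting in the final manuscript". After that, "at least one of the principal investigators will review the AE report" in REDCap and "identify the type of AE and severity based on pre-defined criteria". Events are captured by questions in every patient follow-up questionnaire.
- **Serious events meeting a condition.** "If any serious adverse event (SAE) that interferes with study protocol compliance is identified, it will be reported to the ethics board"; in the same sentence, "the respective chiropractor will be notified, and patients will be instructed to discontinue the study".

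The section also sets up independent oversight: "A Data and Safety Monitoring Board (DSMB) will monitor participant safety, data quality, and the progress of the trial". The board is to keep in frequent email contact, "formally meet every 6 months, and monitor data quality and adverse events".

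**The concern.** The condition in the second tier is whether the event gets in the way of following the protocol. That is a matter of trial conduct. It does not track seriousness, relatedness to treatment or unexpectedness, which are the properties that make an event a matter for an ethics board. A serious event in a patient who goes on answering the text messages and attending visits falls outside the condition.

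Such a patient is also still under treatment. In the maintenance care stratum, pre-planned visits with manual treatment continue at 4 to 12 week intervals; in the control arm, treatment continues at the clinician's judgment. At stake is whether the ethics board, and the clinician who will next treat the patient, learn of the event through the trial's own procedures. The article expects only mild events, so by its own account any serious event would be unexpected.

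**Working it through.** No arithmetic applies: the point rests on no rate, sample size or power figure. The check is to read off who is told in each case, and then to look for any other route.

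**Step 1. Recipients as written in Safety monitoring.**

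| Event | Principal investigators (notice, review, grading, record) | Ethics board | Treating chiropractor | DSMB, individual event |
|---|---|---|---|---|
| Non-serious | Yes | Not stated | Not stated | Not stated |
| Serious, interferes with compliance | Yes | Yes | Yes | Not stated |
| Serious, does not interfere | Yes | Not stated | Not stated | Not stated |

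The first and third rows are identical. A serious event in a compliant patient is thus handled by the same stated route as mild soreness, apart from the severity grade it is given.

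**Step 2. Is there another route to the ethics board?** Safety monitoring says no audit is pre-planned and that the board may choose to audit. That is a possibility, not a report. Protocol amendments and Ethical considerations concern changes to the protocol and approval and consent, not events. Provisions for post-trial care plans no follow-up, because only mild transient effects are expected.

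**Step 3. Is there another route to the chiropractor?** Adverse events are collected in the patient questionnaires. The clinician column of Table 2 lists implementation data, clinical impression, and visit dates and content; adverse events are not in it. The chiropractor may hear of an event from the patient, but no stated procedure ensures it.

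**Step 4. Is there a route to the DSMB?** Its remit covers adverse events and it is in email contact between meetings. The sentences on notification name the principal investigators, the ethics board and the chiropractor, but not the DSMB. The remit is stated; the step that feeds it is not.

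**Step 5. What does the qualifier govern?** One condition controls three consequences in one sentence: the report to the ethics board, the notice to the chiropractor and the instruction to discontinue. Interference with compliance could bear on the third; it has no evident bearing on the first two. The drafting may have merged two rules. Because they share the qualifier, deleting it outright would also widen the instruction to discontinue.

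**The case against.** The strongest case on the other side has four parts.

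- **Events are not ignored.** A reader might infer that a serious event in a compliant patient leads to nothing. The text does not support that: "the principal investigators will be notified immediately via email for documentation and reporting in the final manuscript", followed by review and grading. This stands in full. The harms data for the final report are not lost; what is missing is escalation beyond the investigators.
- **The DSMB has a safety role.** A reader might infer that the DSMB is shut out, or hears of an event only at its 6-monthly meeting. The article says otherwise about its remit and its email contact, so no delay can be derived. How individual events reach the DSMB is also detail that a condensed article may leave to the full protocol or a charter. This largely stands, and it makes the DSMB limb secondary.
- **The breadth of the filter is unknown.** Interference is not defined, and a hospital stay could itself disturb visits or questionnaires and so meet the condition. The text gives no route for other serious events, but it does not forbid reporting them. A reader might try to size the gap from the 20% dropout allowance in the Sample size section. That allowance concerns retention, not compliance after a serious event, and cannot be used in this way.
- **It is a condensed article.** This defence does not reach the main point. The article does not stay silent on reporting to the ethics board; it states a rule with a restrictive condition. If the full protocol reports all serious events, the article misstates it. If it does not, the gap is real. The sentence needs correction either way.

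**Conclusion.** The point holds in a limited form. As written, reporting a serious event to the ethics board and notifying the treating chiropractor depend on interference with protocol compliance and not on seriousness. For a serious event in a patient who stays compliant, investigator notification, review, grading and documentation are the only steps stated. The absence of a stated step to the DSMB for individual events is a weaker, secondary point.

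The size is qualitative. The article gives no rate of serious events and expects only mild ones, so the number affected is probably small, but each would be an unexpected event. No estimate, test or sample size changes. The conclusion assumes that the sentence is followed as worded and that no document not shown overrides it. It implies no view on when a patient should leave the study. It is worth correcting now: the Trial status section has recruitment running to May 2026 and data collection to July 2027.

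**What to change.** Split the sentence so that reporting and discontinuation are separate rules.

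1. **Reporting.** State that every serious adverse event the investigators identify is reported to the ethics board and to the DSMB, and notified to the treating chiropractor, whether or not it affects protocol compliance. If a DSMB charter already provides for its notification, refer to it.
2. **Discontinuation.** Keep this wording, with its present condition, in a sentence of its own and unchanged by this edit. The sponsor should reconcile it separately.

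The cost is a short amendment under the route in the Protocol amendments section, which covers changes that may affect patient safety, plus additional recipients on the notifications and a small number of extra reports. No analysis changes.
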